## Abstract

**Background:**

Coronary artery bypass grafting (CABG) is a common surgical treatment for coronary artery disease. The saphenous vein’s advantageous anatomical features make it a popular choice for graft vessels. However, saphenous vein harvesting often results in lower limb complications such as edema, poor scar healing, pain, and reduced functional mobility. These issues can delay recovery and diminish quality of life. Early rehabilitation using leg cycle ergometry may improve outcomes, but comparative evidence with conventional physiotherapy in Phase I post-CABG care is limited.

**Aim:**

To determine the relative benefits of leg cycle ergometry training for CABG patients with saphenous vein graft in phase 1 in terms of scar healing, muscle strength, functional ability, and quality of life.

**Objectives:**

To evaluate the comparative efficacy of leg cycle ergometry exercise versus conventional physiotherapy on scar healing, muscle strength, functional capacity, and quality of life in CABG subjects with saphenous vein grafts during Phase I rehabilitation.

**Methods:**

A randomized controlled trial will be conducted at Shalini Tai Meghe Super Speciality Centre with 70 CABG patients aged 45–65 years. Participants will be randomly allocated to Group A (conventional physiotherapy) and Group B (leg cycle ergometry with physiotherapy) for a 10-day intervention. Outcome measures include the Vancouver Scar Scale, Manual Muscle Testing, 6-Minute Walk Test, and Patient Health Questionnaire-9 (PHQ-9). Data will be analysed using the Mann-Whitney U test and the Wilcoxon signed-rank test; p<0.05 was deemed statistically significant.

**Results:**

As this is a study protocol, no results are available yet. It is hypothesized that leg cycle ergometry, when added to conventional physiotherapy, will lead to greater improvements in scar healing, lower limb strength, functional capacity, and short-term quality of life during Phase I cardiac rehabilitation following CABG surgery.

**Trial registration:**

Clinical Trial Registry-India (CTRI/2025/03/084291). Registered on 15 April 2025.

**Supplementary Information:**

The online version contains supplementary material available at 10.1186/s13063-025-09255-1.

## Introduction

Coronary artery bypass grafting (CABG) is foundational to managing multivessel coronary artery disease. Although saphenous vein grafts (SVGs) may be considered for non-LAD targets, the right ITA (RITA) and radial artery (RA) are associated with improved outcomes [1]. Post-operative cardiopulmonary health is severely compromised with impaired pulmonary and respiratory function mediated by such factors as chest wall pain, decreased respiratory muscle strength, reduced exercise capacity and exercise tolerance, and anxiety with the resumption of more vigorous physical activity [2]. CABG remains one of the most commonly performed cardiac surgeries worldwide, yet post-operative complications continue to influence early recovery and hospital outcomes. Physiotherapy in the ICU was recently incorporated and is starting to work on the concept of early mobilization, as well as its importance in the practice of early mobilization [3]. Structured ICU exercise prescription helps prevent respiratory complications, preserve muscle strength, reduce mortality and disability risk, and promote psychological well-being. The objectives of cardiac rehabilitation (CR) are to promote independence, psychological stability, stress reduction, social reintegration, and restoration of physical capacity [4]. CR is a multidisciplinary, individualized program that addresses the functional and physiological limitations of patients recovering from heart disease [5, 6]. As a fundamental part of every cardiac rehabilitation program (CRP), regular physical activity can improve functional work capacity in cardiac patients after coronary artery bypass graft surgery [7]. Supervised exercise-based cardiac rehabilitation (CR) has been strongly recommended in recent years as an important adjunct therapy following CABG, with well-documented benefits associated with improved prognosis after revascularization [8]. Most usual-care CR in bypass patients is based on aerobic training, and an increasing body of literature has recommended the concomitant application of lower limb resistance training to enhance the beneficial effects of CR, including increased skeletal muscle strength (particularly lower limb muscle volume), an important peripheral factor influencing cardiac function [9]. Despite this, the majority of available research has focused on general aerobic training, with limited attention to targeted lower-limb rehabilitation following saphenous vein graft harvesting. CABG patients who undergo saphenous vein graft harvesting frequently experience lower limb complications such as edema, pain, and delayed scar healing, which can limit mobility and hinder participation in early cardiac rehabilitation. Phase I cardiac rehabilitation refers to the early, in-hospital phase of recovery typically spanning the first 2–10 days for after CABG surgery. It focuses on early mobilization, pulmonary care, and gradual restoration of physical function. While international guidelines such as those from the American Heart Association (AHA) and the European Society of Cardiology (ESC) emphasize early rehabilitation, implementation in developing countries like India remains inconsistent due to limited resources and lack of structured physiotherapy frameworks. Although several international trials have assessed aerobic training after CABG, few have specifically focused on targeted lower-limb rehabilitation addressing donor-site recovery, particularly within early Phase I hospital settings. This evidence gap highlights the need for structured, low-cost interventions such as leg cycle ergometry in resource-limited cardiac units. In the Indian healthcare setting, standardized in-hospital CR protocols are still evolving, highlighting the importance of evaluating feasible, evidence-based interventions during this early recovery. Despite the growing emphasis on early rehabilitation, there is a paucity of randomized controlled trials evaluating structured lower-limb exercises, such as leg cycle ergometry, during Phase I recovery in post-CABG patients.

Application of phase 1 cardiac rehabilitation on patients improved patients’ self-efficacy in terms of independence in daily activities, and it also decreased the need for phase 2 CR [10]. Cycling started earlier in a patient’s ICU stay may further improve patient outcomes [11]. It has been shown that a daily cycling exercise (passive and active) can enhance the functional capacity, self-perceived functional status, and quadriceps muscle strength of ICU patients [12]. Leg cycle ergometry, a low-impact closed-chain exercise, enhances peripheral circulation, promotes venous return, and reduces graft-site complications, thereby facilitating faster scar healing and improving lower-limb strength and endurance during early post-CABG recovery. However, evidence regarding its use during Phase I rehabilitation after CABG with saphenous vein graft is scarce. Therefore, this trial aims to compare leg cycle ergometry with conventional physiotherapy to determine their effects on scar healing, muscle strength, functional capacity, and quality of life in post-CABG patients.

The selected outcome measures—Vancouver Scar Scale (VSS), 6-Minute Walk Test (6MWT), Manual Muscle Testing (MMT), and PHQ-9—were chosen to comprehensively evaluate the physical, functional, and psychological dimensions of recovery. Although other tools like SF-36 or EQ-5D exist, these outcomes are particularly sensitive to short-term Phase I rehabilitation changes. By targeting both early physical recovery and graft-site healing, this study provides a novel and clinically relevant approach to postoperative cardiac rehabilitation, with the potential to inform physiotherapy practices and hospital protocols across similar settings. These outcomes collectively represent the biopsychosocial recovery model essential to modern rehabilitation research.

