#### Inclusion criteria

Adults aged 45–65 years of either sex.Patients who have undergone elective CABG surgery using a saphenous vein graft.Hemodynamically stable, conscious, and oriented patients within 1–10 days post-surgery.Participants who provide written informed consent.

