#### Outcome measures

All outcomes will be assessed at two time points: baseline (post-operative day 1–2, before intervention) and at the end of the 10-day Phase I rehabilitation period (post-operative day 10). Assessments will be conducted by blinded physiotherapists in the hospital setting.

This trial has two co-primary outcomes: (1) scar healing measured by the Vancouver Scar Scale and (2) functional capacity measured by the 6-Minute Walk Test. Secondary outcomes include muscle strength (MMT) and quality of life (PHQ-9).

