#### Secondary outcome measures

Quality of life-PHQ-9: The Patient Health Questionnaire-9 (PHQ-9) is a validated screening tool for depressive symptoms. Scores of 5–9, 10–14, 15–19, and ≥20 indicate mild, moderate, moderately severe, and severe depression, respectively. This measure captures the psychological dimension of recovery, which can influence engagement and adherence during early rehabilitation.Manual muscle testing: Manual Muscle Testing assesses voluntary muscle strength against graded resistance (Grades 0–5). The examiner stabilizes the limb and applies resistance to determine maximal effort. It provides a practical, reproducible assessment of lower-limb strength when instrument-based testing is not feasible in post-surgical patients.

Together, these outcome measures represent the biopsychosocial recovery model, capturing scar healing (tissue integrity), functional performance (6MWT), muscular strength (MMT), and emotional well-being (PHQ-9). The chosen tools are particularly suitable for short-term, hospital-based Phase I cardiac rehabilitation and have established validity and reliability in this population.

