## Discussion

Coronary artery bypass grafting remains one of the most performed and effective revascularization procedures, yet donor-site complications from saphenous vein harvesting such as edema, pain and delayed scar healing can significantly restrict early mobility and delay recovery. Early rehabilitation and mobilization are vital to reduce postoperative functional decline and improve hospital outcomes. Leg cycle ergometry, a closed chain rhythmic exercise, can enhance venous return, improve peripheral circulation, and maintain muscle activation without imposing excess cardiac stress. Incorporating LCE during Phase I cardiac rehabilitation may therefore promote graft site healing, preserve lower limb strength and accelerate functional independence. The selected outcome measures—Vancouver Scar Scale (VSS), 6-Minute Walk Test (6MWT), Manual Muscle Testing (MMT), and PHQ-9—collectively capture the multidimensional nature of recovery. VSS evaluates donor site tissue integrity, 6MWT and MMT reflect physiological and functional capacity, while PHQ-9 captures short-term psychological well-being that influences adherence to rehabilitation. Earlier studies, such as those by Hirschhorn et al. [13] and Hamid et al. [10], demonstrated the safety and feasibility of early ergometry in CABG patients but did not assess localized donor-site outcomes or psychological domains. Hence, this trial addresses an important evidence gap by integrating lower-limb-specific intervention and comprehensive outcome evaluation within the early post-CABG recovery phase, especially in an Indian tertiary-care setting where structured Phase I cardiac rehabilitation is still developing.

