### Data collection method

All participants will be enrolled and baseline data collected on post-operative day 1–2, followed by a 10-day in-hospital Phase I cardiac rehabilitation program (post-operative day 2–11). Assessments will be performed by blinded physiotherapists at the specified time points according to the SPIRIT 2013 schedule shown in Fig. 2 (Supplementary no.3).

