### Statistical methods

All statistical analyses will be performed using IBM SPSS Statistics version or equivalent software. Descriptive statistics will be used to summarize demographic and baseline characteristics, with continuous variables expressed as mean ± standard deviation and categorical variables presented as frequencies and percentages. The Shapiro–Wilk test will be applied to assess data normality. For within-group comparisons (pre- and post-intervention), the paired t-test will be used for normally distributed data, while the Wilcoxon signed-rank test will be applied for non-parametric data. Between-group comparisons (experimental versus control) will be conducted using the independent t-test for normally distributed data and the Mann–Whitney U test for non-parametric data. Analysis of covariance (ANCOVA) will be employed to adjust for any baseline differences between groups. Missing data will be addressed using an intention-to-treat approach, applying the last observation carried forward method where appropriate. In addition, subgroup analyses may be performed based on age, sex, and baseline functional capacity to explore potential secondary interactions. A p-value of <0.05 will be considered statistically significant for all analyses.

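### Assuming a recall of 7–14 days, a PHQ-9 taken on post-operative day 1–2 describes mainly the time up to and including surgery, so its within-group change cannot be read as change during the programme

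*Protocol article*

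**What the plan says.** The Outcome measures section of the protocol article fixes two assessments for every outcome: "baseline (post-operative day 1–2, before intervention) and at the end of the 10-day Phase I rehabilitation period (post-operative day 10"). It gives PHQ-9 a secondary role: "Secondary outcomes include muscle strength (MMT) and quality of life (PHQ-9"). The Secondary outcome measures section describes it thus: "The Patient Health Questionnaire-9 (PHQ-9) is a validated screening tool for depressive symptoms". That section then lists the usual severity bands, but gives no recall period and mentions no modified one.

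Two places present PHQ-9 as a measure of short-term change. The Introduction justifies the four measures over SF-36 and EQ-5D with the statement that "these outcomes are particularly sensitive to short-term Phase I rehabilitation changes". The Discussion adds that "PHQ-9 captures short-term psychological well-being that influences adherence to rehabilitation".

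The Statistical methods section plans paired tests for all outcomes: "For within-group comparisons (pre- and post-intervention), the paired t-test will be used for normally distributed data", with the Wilcoxon signed-rank test otherwise. Between arms it plans an independent t-test or a Mann–Whitney U test, and it brings in ANCOVA to adjust for any baseline differences.

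**The concern.** A questionnaire that asks about a past period measures that period, not the day on which it is filled in. If PHQ-9 is completed one or two days after surgery, most of what it asks about happened before or on the day of the operation. The paired comparison then sets mood from mainly before surgery against mood from a later period. The operation itself lies between the two, as well as the programme.

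PHQ-9 is the only instrument behind the quality-of-life objective, and the Discussion names psychological outcomes among the benefits that could support routine use of ergometry. A significant paired test could be taken as psychological benefit of rehabilitation when it partly reflects having had surgery. If the final score also looks back past the start of the programme, a null difference between arms could be taken as absence of effect when the contrast was only weakened.

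**Working it through.** **Inputs**

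- Baseline day b = POD 1 or 2, final day e = POD 10 (Outcome measures).
- Alternative final day e = POD 11. The Data collection method section describes baseline on POD 1–2 "followed by a 10-day in-hospital Phase I cardiac rehabilitation program (post-operative day 2–11"), and ten consecutive days starting on POD 2 end on POD 2 + 9 = POD 11.
- Recall length L is **not in the document**. L = 14 days is assumed as the usual form, and 7–14 days is shown as the range.
- Day 0 is the day of surgery. A window of L days ending on day t covers days t − L + 1 to t.

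The plan has no figure of its own to reproduce here beyond the interval between assessments: e − b = 10 − 2 = 8 to 10 − 1 = 9 days, or 9 to 10 days with e = 11.

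**Formulas**

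- Baseline days on or before surgery: L − b; share (L − b)/L.
- Days shared by the two windows: max(0, L − (e − b)).
- Final-window days on or before surgery: max(0, L − e).

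**Results**

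| L | b | Baseline days on or before surgery | Share | Shared days, e = 10 | Shared days, e = 11 | Final-window days on or before surgery, e = 10 / e = 11 |
|---|---|---|---|---|---|---|
| 14 | 1 | 13 | 93% | 5 | 4 | 4 / 3 |
| 14 | 2 | 12 | 86% | 6 | 5 | 4 / 3 |
| 10 | 1 | 9 | 90% | 1 | 0 | 0 / 0 |
| 10 | 2 | 8 | 80% | 2 | 1 | 0 / 0 |
| 7 | 1 | 6 | 86% | 0 | 0 | 0 / 0 |
| 7 | 2 | 5 | 71% | 0 | 0 | 0 / 0 |

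**How far each statement depends on L**

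1. The baseline is mainly on or before the day of surgery when (L − b)/L > 1/2, that is, L > 2b. With b = 2 this needs L above 4 days, so it holds throughout the assumed range.
2. The windows overlap only when L > e − b, that is, above 8–9 days for e = 10 or 9–10 days for e = 11. This holds at 14 days and fails at 7.
3. At L = 14 and e = 10, the part of the final window that lies after baseline is 8/14 = 57% to 9/14 = 64%. With e = 11 it is 9/14 = 64% to 10/14 = 71%. At L = 7 it is 100%.

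**What each test then compares**

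The paired test contrasts a window that is 71–93% pre-operative or operative with one that lies wholly or mostly after baseline. The operation and the programme are therefore confounded in it. The between-arm test compares final scores with the same window in both randomised groups, so days before treatment enter both arms alike. They can shrink a real difference but cannot create one.

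**The case against.** The strongest reply has four parts.

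- **The recall length is not in the article.** A reader might infer that the look-back is simply longer than the gap between assessments. The document does not support that as a fact. It is true at 14 days and false at 7, and a condensed article normally leaves form wording to case report forms. This stands, and the overlap and attenuation are therefore conditional. The content of the baseline window is much less so, because it needs only a recall above 4 days.
- **The comparative question survives.** A reader might also infer that PHQ-9 cannot show psychological recovery at all. That is too strong: even at 14-day recall, 57–64% of the POD 10 window lies after baseline. The randomised contrast remains valid, and a baseline that reflects mood before treatment is a proper covariate. This stands fully.
- **Paired change is confounded with natural recovery for every outcome here.** This is true. For PHQ-9, however, the baseline window additionally reaches back before the operation, so the starting point is not the post-operative state that a reader would take it to be. Nothing in the article says that the PHQ-9 change will be reported as a treatment effect; that risk is a matter of interpretation.
- **Timing varies.** The Inclusion criteria admit "Hemodynamically stable, conscious, and oriented patients within 1–10 days post-surgery", so some baselines could fall later. With L = 14, a baseline on POD 7 would be exactly half pre-operative or operative (7/14), and later ones less. At L = 7 the balance tips by POD 4 (3/7 = 43%). But Outcome measures and Data collection method both place baseline on POD 1–2.

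A loss of power could be calculated from the dilution, but only by assuming equal weight for each day, an unchanged standard deviation and a constant effect from the first session. The document supports none of these, so no such figure is given.

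**Conclusion.** The point holds in a limited form. With baseline on POD 1–2 and a recall of 7–14 days (assumed), 71–93% of the baseline PHQ-9 window falls on or before the day of surgery. The planned paired test cannot be read as change during the programme, and the Introduction and Discussion overstate how well the measure follows short-term change in this schedule.

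If the recall is 14 days, the two windows also share 5–6 days (4–5 if the final assessment is on POD 11), and the between-arm difference may be attenuated. If it is 7 days, there is neither overlap nor attenuation. In both cases the recall window does not bias the randomised comparison towards either arm.

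This concerns one secondary outcome and its interpretation. The POD 10 and POD 11 end dates need to be reconciled in the protocol, but the conclusion is the same for both.

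**What to change.** In Statistical methods, for PHQ-9:

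- Drop the paired pre-post test, or state that it will not be interpreted as an effect of the programme.
- Base inference on the between-arm final score by ANCOVA with baseline PHQ-9 as a covariate in all cases, not only when the arms appear to differ at baseline.

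In Secondary outcome measures, state the recall period of the form in use and label the baseline score as pre-/peri-operative mood. If the recall is two weeks, add that a null difference between arms is not by itself evidence of no psychological effect, because part of the final window precedes treatment.

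Do not change the recall wording of the form now. Recruitment began in June 2025 according to Trial status, and a change would leave two versions of the outcome in one trial.

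The cost is a wording change and the loss of one secondary within-group p-value. No new data are needed, and the ANCOVA is already among the planned methods.

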## Trial design

This study will follow a single-centre, parallel-group, randomized controlled trial design with an allocation ratio of 1:1. Participants will be randomly assigned to either the leg cycle ergometry plus conventional physiotherapy group or the conventional physiotherapy-only group.

The randomization sequence will be computer-generated using block randomization and implemented through sealed, opaque envelopes prepared by an independent researcher who is not involved in participant recruitment or assessment.

Because of the nature of the intervention, participants and treating physiotherapists cannot be blinded. However, all outcome assessors and data analysts will remain blinded to group allocation to reduce measurement bias.

The study will be conducted at a single tertiary-care teaching hospital with a dedicated cardiac rehabilitation unit. The trial follows the SPIRIT 2013 (Standard Protocol Items: Recommendations for Interventional Trials) guidelines for reporting clinical trial protocols and has been prospectively registered with the Clinical Trial Registry of India (CTRI/2025/03/084291) (Supplementary A). The planned CONSORT flow chart of participant recruitment and randomization is presented in Fig. 1.

**Fig. 1 Fig1:**
[figure not shown]
Planned CONSORT flow chart

Final analysis will include all participants completing the study per protocol and intention-to-treat principles.

This diagram outlines the projected flow of participants through the study in accordance with CONSORT 2010 guidelines. Actual participant numbers and reasons for exclusion will be updated upon study completion.

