### Sample size calculation

The sample size was calculated in consultation with the institutional biostatistician using Cohen’s formula for comparing two independent means (Cohen, 1988), assuming an effect size (d) = 0.49, α = 0.05, and power (1–β) = 0.80.

Parameter estimates were derived from previous studies with comparable rehabilitation protocols in post-CABG patients [10, 13], the estimated sample size was 35 participants per group. Allowing for a 20% dropout rate, the final sample size was adjusted to 42 participants per group, resulting in a total of 84 participants.

The chosen effect size of 0.49 represents a moderate clinical difference expected in primary outcomes such as functional capacity, scar healing, and quality of life. This sample size is therefore adequate to detect a meaningful difference between groups in early post-CABG recovery.

$$\mathrm{n}=\mathrm{d2}(2(\mathrm{Z}\upalpha /2+\mathrm{Z}\upbeta)2 \cdot (2{\upsigma}2))=35$$

Mean group 1 (M1): 5.53

Standard deviation group 1: 1.75

Mean group 2 (M2): 4.60

Standard deviation group 2: 2.00

Correlation between groups: 0.5 10

Effect size: 0.49

Alpha level: 0.05 Power (1-beta): 0.8

Sample size- 35 in each group

Drop out 20%= 20x35/100=7 35+7=42

The revised sample size is 42 in each group

The total sample size required = 84 subjects (42 subjects in each group)

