### Data management

Data collection and reporting will be overseen by the principal investigator and verified by an independent quality monitor. All research documentation will be cross-checked twice for accuracy. After data collection, groups will remain blinded during data entry and cleaning. The final Excel dataset will be reviewed by an allocation-blinded statistician for analysis. Data will be stored in a secure, password-protected, access-controlled server located at Datta Meghe Institute of Higher Education and Research.

Participant data will be anonymized using coded identifiers, and no personal details will appear in reports or publications. Backup copies will be maintained on encrypted drives to prevent data loss.

Participation is voluntary; participants may withdraw at any time. If consent to use existing data is denied, such data will be permanently deleted.

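### The note to Fig. 1 limits the final analysis to completers yet calls it intention-to-treat, conflicts with the Statistical methods section, and names no primary analysis set

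*Protocol article*

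**What the plan says.** Two places in the Protocol article bear on who is analysed.

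- **Trial design, note to Fig. 1:** "Final analysis will include all participants completing the study per protocol and intention-to-treat principles". The same note adds: "Actual participant numbers and reasons for exclusion will be updated upon study completion".
- **Statistical methods:** "Missing data will be addressed using an intention-to-treat approach, applying the last observation carried forward method where appropriate". Here intention-to-treat appears only as a way of handling missing data. The section does not say that all randomised participants are analysed as allocated, and it ties no analysis set to an outcome.

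Three other statements matter for the consequences.

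- **Outcome measures:** "This trial has two co-primary outcomes: (1) scar healing measured by the Vancouver Scar Scale and (2) functional capacity measured by the 6-Minute Walk Test". There is one baseline and one end-of-programme assessment, with nothing between.
- **Data management**, on participants who withdraw: "If consent to use existing data is denied, such data will be permanently deleted".
- **Sample size calculation:** a 20% dropout allowance takes 35 per group to 42, or 84 in total.

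No section defines a per-protocol set or ranks it against intention-to-treat.

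**The concern.** A set made up of those who complete the study is a completer set. An intention-to-treat set contains everyone randomised, in the group to which they were allocated. The Fig. 1 note puts both labels on a single final analysis, and what it literally includes is completers.

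Two things are at stake. First, an analysis that leaves out randomised participants no longer compares the groups that randomisation formed. If those who leave tend to do worse, and more of them leave one arm, that arm's remaining participants look better than the arm as a whole. Differential loss is plausible here: the exercise programmes differ between arms, participants and therapists are unblinded, and the protocol lists symptoms that end a session or pause exercise. Second, with two populations available and neither named primary, the choice can be made after the results are known.

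**Working it through.** **1. The two passages side by side.** Take a randomised participant with a baseline value and no end-of-programme value.

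| Source | Treatment of this participant |
|---|---|
| Fig. 1 note, read literally | Not a completer, so not in the final analysis |
| Statistical methods | Kept, with the last observation carried forward where that is judged appropriate |

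Because outcomes are taken only twice, the last observation for this participant is the baseline value. One reading deletes the participant; the other enters them as unchanged since before the programme. For walk distance early after surgery, these can give different estimates.

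**2. How many participants are affected.** Inputs are from Sample size calculation: 35 per group, 20% dropout, 84 in total.

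- The plan's own allowance: 0.20 × 35 = 7 per group; 35 + 7 = 42; 2 × 42 = 84. This reproduces. It implies 2 × 7 = 14 non-completers, leaving 70.
- 20% applied to all who are randomised: 0.20 × 84 = 16.8, about 17, leaving 67.2, or 33.6 per arm.

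So 14 to 17 participants move in or out with the reading. Whether 35 per group follows from the stated method is a separate question, and nothing here depends on it.

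**3. Possible bias of a completer analysis.** Suppose a proportion p of an arm does not complete, and non-completers do worse than completers by δ (in SD units). If the arm's full mean is μ and the completers' mean is x, then μ = (1 − p)x + p(x − δ) = x − pδ, so x = μ + pδ. With the same δ in both arms, the between-group difference is biased by

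bias = δ × (p_A − p_B).

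The protocol gives neither δ nor dropout by arm. Both are assumed below, with average dropout held at 20%.

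| Dropout by arm | δ = 0.25 | δ = 0.5 | δ = 1.0 |
|---|---|---|---|
| 20% v 20% | 0 | 0 | 0 |
| 25% v 15% | 0.025 | 0.05 | 0.10 |
| 30% v 10% | 0.05 | 0.10 | 0.20 |

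The planning effect is d = 0.49. Against it, 0.025 is about 5% (0.025/0.49), 0.10 about 20%, and 0.20 about 41%. The zero row needs equal dropout and an equal deficit in both arms.

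**The case against.** The best defence has four parts.

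- **Two analyses may be meant.** The sentence can be read as one analysis under each principle, which is common practice and not contradictory. It is also a note to a figure that is not shown, whose boxes might list the sets separately. This reading is fair, so it would go too far to state as fact that one set has been defined as two incompatible populations. But on this reading too, the sentence admits only those completing the study, and neither analysis is named primary.
- **The Statistical methods section leans the right way.** Imputing missing outcomes has little purpose unless participants without a final value are retained. That stands. A reader might infer that the primary result will drop non-completers, but the documents do not support certainty: one passage permits it and the other points away from it. That is a conflict to settle.
- **Completing the study need not mean completing the exercise.** A reader might infer that anyone who stops for symptoms or goes home early is removed. The Intervention section and the note below Table 2 describe ending sessions and pausing or discontinuing exercise, with re-evaluation before resuming. They do not describe leaving the study, and early discharge is not mentioned as a cause of dropout. Someone who stops cycling but is assessed at the end could count as a completer.
- **The size is uncertain.** The plan's allowance is 14; 17 appears only when 20% is applied to all 84. No single bias figure can be read from the protocol, and zero is within the range.

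An unseen analysis plan could name the primary set, and an omission on that score alone would not be a finding. The point here is what the article states: a later plan would have to depart from part of the published sentence.

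**Conclusion.** The Fig. 1 note is wrong as written. It restricts the final analysis to completers while invoking intention-to-treat, it conflicts with the Statistical methods section, and it leaves the primary set open even on the kinder reading. The number of randomised participants whose inclusion depends on the reading is about 14 to 17 of 84, taking the plan's 20% dropout as given.

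The bias is unknown from the documents. Under the assumptions above, with the same deficit in both arms, it runs from zero at equal dropout to 0.20 SD at 30% v 10% dropout with a 1.0 SD deficit. The case for change rests on the contradiction and the open choice of population, not on any one of these illustrative values. It deserves correction because it bears on both co-primary comparisons and is cheap to settle.

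**What to change.** Replace the sentence in the Fig. 1 note with:

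> The primary analysis of both co-primary outcomes includes all randomised participants in the group to which they were allocated, except where consent to use data is withdrawn; a per-protocol analysis, with the set defined by adherence before unblinding, is a sensitivity analysis.

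The consent exception is needed because Data management provides for deletion of such data. Defining the per-protocol set by adherence keeps it distinct from the set of participants who happen to have a final measurement.

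Align the Statistical methods section with this sentence: state the same primary set there, and say how missing end-of-programme values are handled within it, since carrying the last observation forward means carrying the baseline forward in this design. Seek the end-of-programme assessment from participants who stop exercising, so that fewer values need imputing.

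The cost is one sentence, one sensitivity analysis and a small follow-up effort. Recruitment is expected to run to August 2026, so the change can be recorded before any unblinded analysis.
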